### Allocation and blinding

After giving online written informed consent to participate in the study and completing online eligibility and baseline questionnaires, participants who meet the criteria will be randomized to the experimental or the WL control group. An allocation scheme will be created by a member of the research team blind to the study using a computerized random generator (random allocation software 2.0) at a 1:1 ratio. Randomization will be stratified by type of chronic medical condition (diabetes, fibromyalgia, intestinal inflammatory illness, migraines, low-back chronic pain and other conditions). After randomization is completed, both researcher and participant will be informed with the results. Participants in the intervention groups will have access to the program right after receiving the outcome, meanwhile participants in the WL control group will have to wait 3 months to have access to the intervention. As both participants and researcher will be informed about which of the two conditions participants are assigned, blinding for the treatment is not possible.

### Statistical methods

The latest version of SPSS (v.26) will be used for all data analysis. T-tests for independent-samples (t), ANOVAs, and chi-square analysis (χ2) will be calculated to investigate the characteristics of the randomized sampled and included in the RCT and to explore group differences in participants’ sociodemographic (e.g., age, gender) and clinical data (e.g., quality of life, well-being). Attrition and dropout rates will be calculated by reporting percentages and patterns of missing data. Intent-to-treat mixed-model analyses without any ad hoc imputations will be used to handle missing data in case of participant dropout and to conduct the efficacy analysis [73]. This analysis compares the study groups based on the treatment to which they were randomly allocated. It does not assume that the last measurement is stable, it does not involve any substitution of missing values with supposed or estimated values, it is conducted using all available observations, thus reducing the biases and loss of power caused by the simple deletion or random imputation of incomplete data. Mixed-model analyses are appropriate for RCTs with multiple time points and pre-post designs, and it has showed remarkable robustness to violations of distributional assumptions (e.g., skewed, kurtosis, or heteroscedastic) [74, 75]. To study distributional assumptions and the impact of missing random effect components on model some test will be included: Normality assumptions will be explored using the Shapiro-Wilk test (for each experimental group, N < 50), the Kolmogorov-Smirnov (K-S) test (for the total sample, N > 50), skewness and kurtosis indices, and normality plots (Q-Q plots). Homoscedasticity will be explored by Levene’s test and Box’s M test for equivalence of covariance matrices. Wald statistic (or Z-test) will be conducted to test the residual error variance estimation and the null hypothesis of homogeneity of residuals. The assumption that data is missing completely at random (MCAR) will be evaluated using Little’s MCAR test. it is robust to violations of distributional assumptions. A linear mixed-effect model for each outcome measure will be implemented using the MIXED procedure with one random intercept per subject. An identity covariance structure will be specified to model the covariance structure of the intercept. For each outcome, time (baseline and 3- and 6-month follow-up) will be treated as a within-group factor and group (experimental and control group) as a between-group factor and significance effects will be followed up with pairwise comparisons (adjusted by Bonferroni correction). Cohen’s d effect size and 95% CI will be calculated for within- and between-group comparisons [76, 77]. Sensitivity analyses will be performed to assess the robustness of the findings in terms of different methods for handling missing data (i.e., mixed models with and without imputation, maximum-likelihood estimation, and maximum-likelihood multiple imputation [78]. The means and standard deviations of the acceptability measures of the intervention will be analyzed. For analyses of associations between intervention outcomes, predictors of change and mechanisms of action, several statistical tests such as Pearson’s correlation, multiple regressions and mediation analysis will be performed. In addition, participants’ qualitative responses regarding facilitators and barriers to the intervention will be explored using a qualitative content analysis and coding and categorization approach to the data using word frequency counts with ATLAS.ti software.

The state of the art of analytic methodology for RCT will be reviewed before analyzing the data, in order to apply the most appropriate statistical analysis procedure.

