### Sample size

The sample will be composed of 68 participants as minimum. The sample size was calculated using the G*Power 3.1.9.7 for Windows program [68]. Estimated sample size was decided based on medium effect sizes (d = 0.4), statistical power of .80 and α = .05, indicating a necessary sample of 52 participants [69]. Considering that the dropout rate in Internet-based interventions for the chronic medical ill population is usually around 30%, a target of 34 people per group was set [70–72].

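### The Wald Z test named for homogeneity of residuals tests whether the residual variance is zero, so it rejects in essentially every dataset of this size and says nothing about homogeneity

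*Protocol article*

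**What the plan says.** All of this is in the Statistical methods section of the protocol article, apart from the sample size.

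- Model: "A linear mixed-effect model for each outcome measure will be implemented using the MIXED procedure with one random intercept per subject". For the random effect, "An identity covariance structure will be specified to model the covariance structure of the intercept". The fixed part is a group-by-time layout: "time (baseline and 3- and 6-month follow-up) will be treated as a within-group factor and group (experimental and control group) as a between-group factor". No residual variance specific to a visit or an arm is described.
- Checks on variance: "Homoscedasticity will be explored by Levene’s test and Box’s M test for equivalence of covariance matrices". The next sentence adds that a "Wald statistic (or Z-test) will be conducted to test the residual error variance estimation and the null hypothesis of homogeneity of residuals".
- Software: "The latest version of SPSS (v.26) will be used for all data analysis".
- Size, from the Sample size section: "The sample will be composed of 68 participants as minimum", which is 34 per arm.

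The same section states that mixed models are robust to heteroscedastic data. It attaches no action to the result of any of these checks.

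**The concern.** The sentence names a test and states its null, and the two do not belong together. A model with one residual variance has no parameter that measures heterogeneity. The only Wald Z available for its residual term asks whether that variance is zero, which is false for any self-report scale.

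A reader of the results would be told that homogeneity was tested and rejected, outcome after outcome, when it had not been tested. The model also assumes equal residual variance at baseline, 3 months and 6 months. The other two named checks, as normally run, do not examine that assumption: Levene's test compares arms at a visit, and Box's M compares covariance matrices between arms.

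**Working it through.** **Inputs.** From the document: 68 participants, 2 arms, 3 visits, random intercept, 30% dropout. Assumed, because the document gives no variances: intercept SD 0.7 (variance 0.49), baseline residual SD 1, normal data. The document gives no figure for the Wald statistic, so there is none to reproduce; the sample size enters only through the degrees of freedom.

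**Step 1: what the Wald Z equals.** With complete data and a positive estimated intercept variance, the REML residual variance is the within-participant mean square, MSE, on df = (N − 2) × 2. Its standard error is MSE × sqrt(2/df). So Z = MSE / [MSE × sqrt(2/df)] = sqrt(df/2), and the data cancel.

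| N with complete data | df | Z |
|---|---|---|
| 68 | 132 | 8.12 |
| 52 | 100 | 7.07 |
| 48 (68 × 0.7, rounded up) | 92 | 6.78 |

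Z passes 1.96 once df exceeds 2 × 1.96² = 7.68. If the intercept variance is estimated at zero, df becomes (N − 2) × 3 = 198 at N = 68 and Z rises to sqrt(99) = 9.95.

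**Step 2: does it respond to heterogeneity?** Simulation with 68 participants, 30% monotone dropout and 300 runs per scenario (intercept and baseline residual SD both 1). The time ratio is the month-6 to baseline residual variance, with month 3 halfway between.

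| True residual variances | Median Z | Rejects |
|---|---|---|
| Equal | 7.15 | 100% |
| Arm ratio 4 | 7.20 | 100% |
| Arm ratio 9 | 7.28 | 100% |
| Time ratio 4 | 7.32 | 100% |
| Time ratio 9 | 7.40 | 100% |

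A valid test of homogeneity would reject about 5% of the time in the first row. In the same runs, Levene's test between arms at 3 months rejected 4% under equal variances, 60% at arm ratio 4 and 96% at arm ratio 9. At time ratios 4 and 9 it rejected 2% and 5%, so it does not see heterogeneity that both arms share.

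**Step 3: what unseen heterogeneity would do to the 3-month between-arm contrast.** With complete data and equal arms, the single-variance model uses P = 0.49 + the mean residual variance over all arm-by-visit cells. The true figure is T = 0.49 + the mean residual variance of the two arms at month 3. The false-positive rate is about 2 × [1 − Φ(1.96 / sqrt(T/P))].

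| Residual SDs at baseline, 3, 6 months | P | T | T/P | False-positive rate |
|---|---|---|---|---|
| Both arms 1, 1, 1 | 1.490 | 1.490 | 1.00 | 5.0% |
| Both arms 1, 1.5, 1 | 1.907 | 2.740 | 1.44 | 10.2% |
| Both arms 1, 1.5, 1.5 | 2.323 | 2.740 | 1.18 | 7.1% |
| Both arms 1, 2, 1 | 2.490 | 4.490 | 1.80 | 14.4% |
| Both arms 1, 0.7, 0.7 | 1.150 | 0.980 | 0.85 | 3.4% |
| Treated 1, 1.5, 1.5; waiting list 1, 1, 1.5 | 2.115 | 2.115 | 1.00 | 5.0% |
| Treated 1, 2, 2; waiting list 1, 1, 2 | 2.990 | 2.990 | 1.00 | 5.0% |

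The last two rows follow the design, in which spread rises only once a participant has had access to the programme. They balance for any ratio k: the month-3 average is (k² + 1)/2 and the all-cell average is (3 + 3k²)/6, which is the same. Simulations of 20,000 runs per pattern at 34 per arm agree: about 10%, 7% and 15% for rows 2 to 4, and 4.9% to 5.4% for the last two.

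**The case against.** The strongest reply accepts the mislabelling and disputes that it matters. Most of that reply stands.

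- **No decision depends on the test.** It is one item in a list of distributional checks. A reader might infer that a sound model would be discarded for every outcome. The document says nothing of the kind, and the primary estimate and its confidence interval do not use the Wald Z.
- **Levene's and Box's M tests cover differences between arms.** If treatment widened the spread in the treated arm only, Levene's test at 3 months would address it. One simulation of that pattern found rejection of 36% at an SD ratio of 1.5 and 83% at 2. The gap is confined to heterogeneity across visits that both arms share.
- **Invalid 3-month inference does not follow.** A reader might infer that because the arms start treatment at different times, the 3-month standard errors must be too small. The last two rows of the Step 3 table show that this mechanism leaves the error rate near 5%, and a fall in spread after baseline makes the test conservative.
- **The article is condensed.** The residual structure is not stated and could be set in a fuller plan. A Wald contrast of separate residual variances could indeed test homogeneity, but no model containing such variances is described.
- **Robustness and later review.** The article asserts robustness to heteroscedastic data and says methods will be reviewed before analysis. Neither corrects the null attributed to the test, and a general claim of robustness does not remove the inflation in the month-3-only rows.

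**Conclusion.** The statement is wrong as written. In the model described, the Wald Z tests a residual variance of zero; it is 8.12 at N = 68 with complete data and rejected in every simulated dataset with 30% dropout, with or without heterogeneity. This rests on the model having a single residual variance, which is how the article describes it.

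The consequence is limited to a misleading diagnostic and the lack of a formal check, as the named tests are normally run, of residual variance across visits. The 3-month contrast becomes anti-conservative only if residual spread at 3 months exceeds the all-visit average, as when it rises in both arms: about 7 to 10% at an SD ratio of 1.5, depending on whether month 6 rises too, and 14 to 15% at a ratio of 2 for a month-3-only rise. These rates depend on the assumed intercept SD of 0.7 and on SD ratios that the document does not supply. They show what could go unnoticed and are not a forecast for this trial.

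**What to change.** 1. Remove the Wald Z as a test of homogeneity, or relabel it as a test that the residual variance is zero and draw no conclusion about homogeneity from it.
2. Check homogeneity by a REML likelihood-ratio comparison (2 df) of the stated model with the same model allowing a separate residual variance at each visit, using a REPEATED time statement with a DIAG structure in MIXED. Arm-by-visit variances can be added if wanted. In 400-run simulations under the Step 3 assumptions, with 0% or 30% dropout, the 2-df comparison rejected 4 to 5% under homogeneity and about 70 to 81% when only the 3-month SD was 1.5 times the others.
3. Report the visit-specific variances, and show the heterogeneous-variance fit with Satterthwaite degrees of freedom as a sensitivity analysis. It should not become a data-driven switch of the primary model.

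The cost is one sentence of wording and one extra MIXED run per outcome, with two more variance parameters in the sensitivity model. No new data or participants are needed.

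### The stated efficacy model uses the baseline inefficiently, leaves out the stratification factor, and rests on a single-correlation covariance that could mis-size the 6-month contrasts

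*Protocol article*

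**What the plan says.** Under Allocation and blinding, the protocol states: "Randomization will be stratified by type of chronic medical condition". Six categories follow, one of them a residual group of other conditions. The list is generated "using a computerized random generator (random allocation software 2.0) at a 1:1 ratio".

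Under Statistical methods, the efficacy model is written out: "A linear mixed-effect model for each outcome measure will be implemented using the MIXED procedure with one random intercept per subject". The next sentence adds: "An identity covariance structure will be specified to model the covariance structure of the intercept". On fixed effects, "time (baseline and 3- and 6-month follow-up) will be treated as a within-group factor" and "group (experimental and control group) as a between-group factor". Significant effects are followed by Bonferroni-adjusted pairwise comparisons. The section names no stratum term, baseline covariate or residual covariance structure, and does not say which contrast carries the primary conclusion. The planned sensitivity analyses vary only how missing data are handled.

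Under Research design, the waiting list gets the programme after its 3-month assessment, so month 3 is the last comparison of treated with untreated participants. The Sample size section assumes "medium effect sizes (d = 0.4), statistical power of .80 and α = .05", "indicating a necessary sample of 52 participants", and sets a target of 34 per arm.

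**The concern.** Three features of the written model deserve attention in a trial of this size.

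- **Baseline.** It enters as a response with its own free difference between arms, although randomisation makes the true difference zero. The model therefore spends information on a quantity known by design. A between-arm pairwise comparison at 3 months then ignores each person's starting value, while the group-by-time contrast is a comparison of change. Both are less precise than an analysis that conditions on baseline.
- **Stratum.** A factor that is balanced by design and left out of the model stays in the error term of any comparison made at a single visit.
- **Covariance.** One random intercept, with residuals that are independent and of constant variance, implies one variance and one correlation for all three pairs of visits. If measurements further apart correlate less, standard errors are wrong in opposite directions for the 0-3 and 0-6 month contrasts.

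At stake are avoidable loss of power at 3 months and possible over-claiming of maintenance at 6 months.

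**Working it through.** **Inputs from the protocol.** d = 0.4; alpha 0.05, taken as two-sided because sidedness is not stated; 52 participants before dropout, so 26 per arm; six strata; visits at 0, 3 and 6 months.

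**Assumptions, since the protocol gives no values.** Equal outcome SD at each visit (set to 1); complete data; baseline-to-3-month correlation r from 0.3 to 0.8; strata explaining 5% to 20% of outcome variance; correlations at 0-3, 3-6 and 0-6 months as listed in step 3.

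**The plan's own figure.** 52 is reproduced as a within-between interaction with f = 0.2, two groups, two measurements and correlation 0.5: noncentrality 0.04 × 52 × 2 / 0.5 = 8.32, power 0.807. A paired t-test with d = 0.4 also gives 52 (power 0.808). Neither is a two-sample comparison at one visit, for which 26 per arm gives 29% power.

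**Step 1, baseline.** The relative variance v of the 3-month contrast is 1 for the raw comparison, 2(1 − r) for change, and 1 − r² for ANCOVA or constrained baseline. ANCOVA divided by change is (1 + r)/2, a cut of (1 − r)/2. Power is from the noncentral t with 50 df and noncentrality (0.4/√v) × √(26/2). At r = 0.6 the noncentralities are 1.442 (raw), 1.612 (change) and 1.803 (ANCOVA).

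| r | Variance cut, ANCOVA vs change | Power: raw | Power: change | Power: ANCOVA |
|---|---|---|---|---|
| 0.3 | 35% | 29% | 22% | 32% |
| 0.5 | 25% | 29% | 29% | 37% |
| 0.6 | 20% | 29% | 35% | 42% |
| 0.7 | 15% | 29% | 45% | 51% |
| 0.8 | 10% | 29% | 61% | 65% |

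**Step 2, strata.** Suppose strata explain a share R² of outcome variance and are balanced across arms. A raw 3-month comparison then reports a standard error too large by 1/√(1 − R²): 1.026, 1.054 and 1.118 for 5%, 10% and 20%. At 10%, actual test size is 2 × P(Z > 1.96 × 1.054) = 3.9%. Adjustment makes the standardised effect 0.4/√0.9 = 0.422, with power 32% against about 29% unadjusted. For the group-by-time contrast, a stratum effect that is constant over time cancels from each person's change, so the loss is close to nil with complete data.

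**Step 3, covariance.** With complete data and equal variances, the random-intercept model estimates the variance of a within-person difference as 2(1 − mean r), where mean r averages the three correlations. The true value is 2(1 − r) for the pair of visits concerned. The ratio of reported to true standard error is √[(1 − mean r)/(1 − r)], and type I error is about 2 × P(Z > 1.96 × ratio).

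| Correlations 0-3 / 3-6 / 0-6 | Ratio, 0-3 | Type I, 0-3 | Ratio, 0-6 | Type I, 0-6 |
|---|---|---|---|---|
| 0.6 / 0.6 / 0.6 | 1.00 | 5.0% | 1.00 | 5.0% |
| 0.6 / 0.6 / 0.5 | √(0.433/0.40) = 1.041 | 4.1% | √(0.433/0.50) = 0.931 | 6.8% |
| 0.7 / 0.7 / 0.5 | √(0.367/0.30) = 1.106 | 3.0% | √(0.367/0.50) = 0.856 | 9.3% |

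A complete-data simulation (6,000 replicates, 34 per arm, correlations 0.7/0.7/0.49) agreed: 3.3% at 0-3 months and 9.4% at 0-6 months.

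**The case against.** The strongest reply is that nothing here makes the planned analysis invalid, and much of it does.

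- **Baseline is not ignored.** A reader might infer that the plan makes no baseline adjustment at all. Baseline is a level of time, so the group-by-time contrast corrects for chance imbalance. Measured against that contrast, the gain at r = 0.6 is from 35% to 42%, not from 29%. It narrows to 4 percentage points at r = 0.8. What stands is a loss of efficiency, and the fact that the pairwise between-arm comparison at 3 months lacks that correction.
- **Strata cost little for change.** A reader might infer that omitting strata inflates every between-arm standard error. It does not for the group-by-time contrast. The 3.9% also presumes good balance within strata. With 68 people over six strata (about 11 each) and no blocking described, balance may be weaker and the test size nearer 5%. The point survives for a raw 3-month comparison, which the text does not rule out as the deciding one.
- **Compound symmetry is implied, not declared.** The identity structure is stated for the intercept; no residual structure is named. The waiting list's switch after month 3 changes means and need not change correlations.
- **Detail may sit elsewhere.** A journal article condenses, and the protocol says methods will be reviewed before analysis. That allows a better model but does not commit to one. The point here concerns a model the article does write out.

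**Conclusion.** The point holds as one of precision and specification. The stated model should be improved before analysis, but its group-by-time contrast is a legitimate test.

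The firmest part is baseline: at every correlation examined, the constrained or ANCOVA form beats the change contrast, with variance 10% to 35% lower. The stratum term is a smaller gain, largely confined to a single-visit comparison. The covariance point is conditional. With equal correlations and variances there is no distortion. Under the decaying patterns assumed, the randomised 3-month comparison is conservative and the liberal error falls on 0-6 month contrasts.

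A reader might infer that the efficacy test has an inflated false-positive rate. The documents do not support that, because by month 6 the waiting list has been offered the programme and the efficacy hypothesis is tested at month 3. The liberal error bears on the claims that gains are maintained and that the waiting list improves once treated.

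All correlations and stratum shares are assumptions. The power figures take 26 analysable participants per arm.

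**What to change.** Before the data are analysed, record the following in a dated specification:

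- Name the 3-month between-arm contrast as the primary comparison.
- Fit the three-visit model with baseline means constrained equal across arms, or use ANCOVA on the 3-month value with baseline as covariate.
- Add condition stratum as a fixed effect.
- Use an unstructured covariance over the three visits with a small-sample degrees-of-freedom correction.
- Keep the random-intercept model as the named fallback if this fails to converge.

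The cost is five stratum parameters and six covariance parameters in place of the two that a random intercept and a residual variance need. That is a modest burden with about 52 to 68 participants, though sparse strata and dropout make the fallback worth stating. Baseline values and condition type are already collected, so no participant, visit or questionnaire is added.

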We hypothesize that: (a) iABCT condition will be more efficacious than the WL group in improving quality of life and well-being and other secondary variables at 3-month follow-up; (b) the gains achieved after iABCT will be maintained at 6-month follow-up; and (c) the iACBT will be well accepted in terms of expectations, satisfaction, usability and opinion by the participants; (d) participants in WL group will show an improving quality of life and well-being and other secondary variables at a 6-month follow-up, once they receive the iABCT; (e) improvements in quality of life and well-being scores will be predicted by self-reported self-compassion and secure attachment; (f) frequency of meditation practice will moderate the improvement in quality of life and well-being after receiving the iABCT; and (g) changes in compassion, self-criticism and attachment style will appear as mediators of greatest changes in quality of life and well-being. Regarding objective 7, no specific hypotheses are proposed due to the exploratory nature of the qualitative analyses.

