## Material and methods

### Research design

A two-arm, parallel-group, randomized controlled trial (RCT) will be carried out to determine the effectiveness of the iABCT on improving the quality of life and well-being of a chronic medical illness population by comparing individuals who have access to the intervention with a WL control group.

Participants will be randomly assigned to one of the two conditions: a) intervention group, and b) control group (WL) and will complete different measures at different assessment points: baseline time (pre-assessment), and 3- and 6-month follow-up. Participants of the WL group will receive access to the iABCT once they fulfill the 3-month assessment.

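### The stated test sequence for efficacy draws on 6-month data collected after the waiting list has received iABCT, and no 3-month contrast is named as the test of hypothesis (a)

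*Protocol article*

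**What the plan says.** In the protocol article, Objectives sets the comparison with the waiting list at 3 months, in both objective (1) and hypothesis (a). The 6-month data have a different role. Objective (2) concerns maintenance in the intervention arm, and objective (4) concerns the waiting-list arm after it has been treated. Hypothesis (b) is that "the gains achieved after iABCT will be maintained at 6-month follow-up", and hypothesis (d) expects the waiting list to improve by 6 months once it has had the programme.

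Research design states the crossover: "Participants of the WL group will receive access to the iABCT once they fulfill the 3-month assessment". Intervention estimates that the programme takes eight weeks, so a waiting-list participant can finish it before month 6.

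Statistical methods specifies a linear mixed model with a random intercept for each outcome, in which "time (baseline and 3- and 6-month follow-up) will be treated as a within-group factor and group (experimental and control group) as a between-group factor". It continues: "significance effects will be followed up with pairwise comparisons (adjusted by Bonferroni correction". No 3-month contrast is singled out, and the model description makes no allowance for the control arm being treated by month 6. The section ends by saying that analytic methods will be reviewed before the data are analysed.

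**The concern.** At month 3 the group factor compares iABCT with no intervention. At month 6 it compares early with delayed iABCT. An interaction across baseline, 3 and 6 months has 2 degrees of freedom and pools the single randomised treatment-versus-control contrast with one whose size depends on how far the waiting list has caught up.

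If the pairwise comparisons follow only when that overall test is significant, two things can happen to the main hypothesis on both primary outcomes:

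- A real 3-month effect may never reach the comparison that would show it.
- The overall test may be significant because the arms differ at month 6 only, when hypothesis (a) is false.

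**Working it through.** **Inputs from the protocol article**

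- Sample size: "Estimated sample size was decided based on medium effect sizes (d = 0.4", with "statistical power of .80 and α = .05, indicating a necessary sample of 52 participants". That is 26 per arm before the dropout allowance and 34 per arm as the recruitment target.
- Statistical methods: random intercept per subject, which implies equal correlation r between any two times.
- Allocation and blinding: 1:1.

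**Assumptions.** Outcome SD of 1, two-sided 5% tests, complete data. The article gives no r; 0.6 and 0.5 are used, with a range of 0.3 to 0.7. The 6-month gap is varied.

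**The plan's own figure.** Two calculations give 52:

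- a two-sided paired t-test with standardised change 0.4;
- a group-by-time interaction with two measurements, f = 0.4/2 = 0.2 and r = 0.5. Its noncentrality is 52 × 2 × 0.04/0.5 = 8.32, for a power of 0.807.

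The same interaction with three measurements needs 42, and a two-sample t-test with d = 0.4 needs 100 per arm. The article does not say which calculation was used. Neither route that gives 52 is a test over three time points. The two-measurement route corresponds to a between-arm difference in change of 0.8 SD, so both 0.4 and 0.8 SD are examined.

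**Formulas.** Let D0, D3, D6 be the between-arm differences, D̄ their mean, and n the number per arm.

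- Interaction: λ = (n/2) × Σ(D − D̄)² / (1 − r), on 2 and 2(2n − 2) df.
- 3-month change contrast: λ = n × (D3 − D0)² / [4(1 − r)], on 1 df.

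**Step 1: d = 0.4, r = 0.6, n = 26.**

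Change contrast: λ = 26 × 0.16/1.6 = 2.6, power 0.353 (denominator df 50).

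Interaction with a 6-month gap of 0.2: D̄ = 0.2, Σ = 0.08, λ = 13 × 0.08/0.4 = 2.6. The noncentrality is the same but is spread over 2 df, and power is 0.276. Other gaps:

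| 6-month gap | Interaction λ | Interaction power |
|---|---|---|
| 0 | 3.467 | 0.356 |
| 0.1 | 2.817 | 0.296 |
| 0.2 | 2.600 | 0.276 |
| 0.3 | 2.817 | 0.296 |
| 0.4 | 3.467 | 0.356 |

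The worst case is a gap of half the 3-month effect, with a loss of about 8 points. At full catch-up (gap 0) or none (gap 0.4), the interaction alone loses nothing.

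**Step 2: 0.8 SD at month 3, r = 0.5, half catch-up (gap 0.4).** Here the 1-df contrast uses the mixed model's denominator df.

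| Per arm | λ (both tests) | Interaction power | Direct contrast power |
|---|---|---|---|
| 26 | 8.32 | 0.722 | 0.815 |
| 34 | 10.88 | 0.840 | 0.906 |

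In 40,000 simulated trials, the 3-month contrast was significant but the interaction was not in 10.4% (26 per arm) and 7.2% (34 per arm). Over r = 0.3 to 0.7 the loss runs from about 2 to 11 points.

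**Step 3: full catch-up, 0.8 SD, r = 0.5, n = 26.** The interaction alone has 0.844 against 0.815. Requiring both to be significant gives 0.776.

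**Step 4: no difference at month 3, 0.8 SD at month 6 only, r = 0.5.** The interaction is significant in 0.844 of trials (26 per arm) or 0.931 (34 per arm). When the 3-month contrast must also be significant, the simulated rejection rate is 0.049 at either size.

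**Step 5: if the overall effect were the group main effect** (0.8 SD, half catch-up, 34 per arm, r = 0.5), simulated power is 0.51, because baseline is averaged in.

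**The case against.** The strongest reply is that the article already gives month 6 its proper role. Objective (1) limits the comparison with the waiting list to 3 months, objectives (2) and (4) treat month 6 arm by arm, and no 6-month between-arm efficacy claim is planned. The fitted model yields the 3-month contrast anyway. The text does not use the word interaction, does not say that pairwise tests occur only after a significant effect, and does not say that efficacy will be declared from an overall test. The article is also condensed, and it promises a review of methods before analysis.

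Much of this stands. The interaction and the gate are readings of the text, although natural ones for crossed factors whose significant effects are then followed up. But the factor levels and the testing order are stated, not left out, and they do not match hypothesis (a). A promised review does not correct that.

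Four stronger inferences are not supported:

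- **Inflated false positives for efficacy.** This would need the overall test alone to be read as efficacy, which the article does not say.
- **A small 6-month gap being taken as lost benefit.** Hypothesis (d) itself predicts that the waiting list will improve.
- **Maintenance being concluded from a non-significant test.** The article does not say so, and it promises within-group effect sizes with confidence intervals.
- **A larger power loss.** A baseline-adjusted 3-month contrast has about 42% power in the Step 1 setting, but baseline adjustment is a separate modelling choice. That all these powers are low at d = 0.4 is a matter of sample size.

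**Conclusion.** The point holds as a mismatch between the stated test sequence and hypothesis (a). Data collected after the control condition has ended enter the test that precedes the efficacy comparison. The power cost is modest and depends on catch-up: at worst about 8 points for d = 0.4 (28% against 35%) and about 9 points for 0.8 SD with 26 per arm (72% against 82%). It is nil for the interaction taken alone at full or no catch-up. These figures rest on assumed correlations, equal variances and complete data. The mismatch itself does not depend on them.

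It is a should-fix. The 3-month estimate is not biased by this, and its error rate is not inflated provided the 3-month comparison must itself be significant. What is missing is a rule that makes that comparison the efficacy test.

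**What to change.** In Statistical methods, declare the between-arm difference in change from baseline to month 3, estimated from the same mixed model, as the efficacy test of hypothesis (a) for each primary outcome. State that it is tested directly and does not depend on an overall effect being significant.

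Report the 6-month data as within-arm follow-up under objectives (2) and (4), with confidence intervals and a statement that these changes are uncontrolled. Label any between-arm figure at 6 months, including Cohen's d, as early versus delayed treatment.

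The cost is analysis wording only. No new data, visits or participants are needed.
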